### Ethno-epidemiology sub study

For this phase, a subset of participants, specifically those entering significant transition periods (e.g., retirement), will be invited to take part in two in-depth qualitative interviews: one at the outset of data collection and another 12 months later (see Fig. 1). After providing a separate informed consent for participation, semi-structured interviews will be conducted with a focus of delving deeper and examining the relationship between life stage transition, social isolation and loneliness and health outcomes following an interview schedule (*see Additional file 2)*. Interviews will be conducted via the participants preferred method (phone, online or face-to-face) with verbal or written consent required before the interview proceeds.

Recruitment will proceed iteratively until enough information power is achieved, emphasizing data richness and depth to generate meaningful themes through reflexive thematic analysis, with an anticipated 50 participants to be recruited.

Interviews will be audio-recorded and will be transcribed verbatim by a professional transcription service, with each transcript crosschecked for accuracy by interviewers. Participants will receive a AUD40 gift voucher on interview completion. Several steps will be taken to remove bias, such as emphasizing to interviewees that the researcher is solely interested in their honest thoughts and perspectives, with no right or wrong answers and assuring interviewees that no identifying information will be published.

### Analysis

#### Quantitative data analysis

Descriptive statistics will be used to determine the prevalence of key variables within the cohort. Parametric and non-parametric statistical analysis techniques will be used to examine the correlation between key variables and health outcomes. Generalised estimation equations (GEE) and other statistical techniques ideally suited to correlated data will be used to examine the extent to which different variables and risk factors are associated with later health outcomes. As count data outcomes such as emergency department admissions are likely to have many zero counts and skewed distribution of non-zero counts, negative binomial or zero-inflated negative binomial analysis, or Poisson or zero inflated Poisson depending on if there is over dispersion of data, approaches will be used. Survival/competing survival analysis will be used to examine risk of and time to key health outcomes. GEE and survival analysis will control for a range of confounding factors identified at baseline and at follow-ups. Growth modelling will be used to identify constant and dynamic influences that affect the initiation of health behaviours (intercept trajectory) and the rate (slope of trajectory) of behaviour change over time. This will allow for incorporation of different influences at key ages and stages in the developmental life course of the cohort.

#### Qualitative data analysis

Interview transcripts will undergo thematic analysis, following the phases outlined by Braun and Clarke [59]. This process entails familiarising oneself with the data, coding it, generating initial themes, developing and reviewing themes, refining, defining and naming themes, before the final write-up. An inductive approach will be employed to allow themes to be derived through a data-driven exploration of the dataset. Three interviewers will utilise reflexivity within the inductive thematic analysis, critically reflecting on their own role as researchers within the research process itself. Interviewers will immerse themselves in the interview transcripts to identify themes that emerge naturally from the participants’ interview data. Open discussions within the research team will be undertaken during the thematic development phase. Themes will be actively produced through the systematic engagement of the researchers with the data. Participants’ quotations with some non-identifiable characteristics like gender and age will be used to illustrate the themes, but owing to ethical considerations, after the second interview, no further contact will be made with participants to obtain more feedback.

NVIVO software will be used to facilitate different stages of data analysis. To enhance methodological rigor and transparency, the Consolidated Criteria for Reporting Qualitative Research (COREQ) checklist [60] will be followed in presenting the methods and results.

The qualitative sub-study will provide a unique longitudinal dataset that complements the quantitative data, enriching and guiding future waves of quantitative data collection. As quantitative data identifies participants for the qualitative sub-study, the themes emerging from qualitative interviews will directly inform the direction of quantitative analysis. This iterative process will suggest additional measures for inclusion in subsequent data collection waves, fostering a holistic understanding of participants'experiences.

## Discussion

### Project outcomes

The Beyond 50 study aims to provide new knowledge of risk and protective factors during times of key life transition, to identify and understand how different health and social factors contribute to the development of anxiety, depression and substance use disorders. An ageing population who exhibits unique risk factors for physical and mental health and substance use disorders poses new challenges to healthcare provision. Given the high proportion of older adults in the Frankston and Mornington Peninsula local government areas, this study is ideally positioned to address existing gaps to better understand the association between different health and social factors and healthy ageing. The results of this study can have local and international relevance in understanding how health and social factors contribute to the development of physical and mental health and substance use disorders.

### Strengths and limitations

Strengths of the Beyond 50 cohort study include the diversity of the Frankston and Mornington Peninsula local government areas, which encompasses urban and regional areas with considerable socioeconomic and geographic diversity. This diversity will result in data that represents a broad range of the population and can contribute to an understanding of how physical and mental health and substance use disorders develop across a diverse population. The study includes a range of measures capturing physical health, mental health and substance use, many of which have been validated in older adult populations, providing the opportunity to explore a range of risk and protective factors associated with healthy ageing. The ethno-epi approach being adopted in the qualitative interviews will allow for in-depth understanding and provide a unique insight into individuals’ experiences during periods if key life transition. Data linkage capturing hospital attendances and health outcomes will complement direct data collection over multiple domains including physical and mental health, psychosocial and substance use domains, and will provide a rich understanding of the experiences and outcomes for this cohort.

Although outcomes measured through linked data are not subject to bias due to attrition, attrition is common with longitudinal data collection. To minimise attrition, several cohort maintenance strategies will be implemented including collection of locator form details, personal communication with all participants via phone calls and twice-yearly distribution of newsletters to keep participants updated with study developments. As non-genuine responses can bias results if included in data analysis, the study utilises a robust quality control and data check protocol including both risk minimisation and elimination methodologies, and the likelihood of non-genuine responses being included in the final dataset is extremely low [58]. Incomplete capture of service utilisation may occur as the NCHA Data Platform only captures data for the public health system and not for the private hospitals in the region, one of which contains an emergency department. Peninsula Health reported 98,168 emergency department presentations between 2022–2023 and represents one of the busiest emergency departments in Victoria [25], and while information for emergency utilisation for private emergency departments are not publicly available, the private emergency department in the area has only 14 bays and is expected to represent a very small number of emergency visits compared to the local public health system. Information relating to private emergency department and hospital access will be captured during quantitative data collection (see Table 1) which will mitigate this potential loss of information and allow us to assess the extent to which presentations at these services are missed.

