### Participants

Participants must be aged 50 to 70 years at baseline survey administration and residing in either the Frankston or Mornington Peninsula local government areas, with plans to stay in the area.

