### Data collection

At study outset, three annual ‘waves’ of data collection are planned. Potential participants will be provided with a participant information sheet detailing the purposes and procedures of the study, including the various methods in which participation can occur (i.e. self-administered online, phone interview or face-to-face). Prior to data collection commencing, participants will need to provide informed consent for participation in the study. Participants will be followed up at 12- and 24-months post completion of baseline survey, via their preferred method of contact and invited to complete follow up interviews via their preferred mode of delivery. Upon completion of each survey, eligible participants will receive a AUD40 gift voucher, with all data collected being stored in a de-identified manner. All contact details and identifying information is stored separately on secure servers.

Study data will be collected and managed using REDCap (Research Electronic Data Capture) [29] and hosted and managed by Helix (Monash University).

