### Data-linkage

The Frankston and Mornington Peninsula local government areas offer the unique advantage of enabling data linkage through the NHCA Healthy Ageing Data Platform, which provides comprehensive healthcare data from all public hospitals, community health and outpatient clinics provided by Peninsula Health [55]. Data from over 11 different datasets are brought together, internally linked within the Peninsula Health data centre and is updated on a weekly basis. Environmental data such as walkability, greenery and parks data has also been incorporated into the Platform. Data linkage will provide up to 10 years of historical data prior to the participants enrolment and a minimum of five years for prospective health outcome data [56], with the potential to extend this into the future pending further funding.

Data obtained through interviews will be linked to participants’ de-identified health data through the NCHA Data Platform, for all attendances to Peninsula Health run services (inpatient and community based). A two-stage, privacy preserving data linkage model will be used in which identifying data in the form of full name, residential address, date of birth, gender and date of death (if applicable) will be extracted from the cohort study contact details database and submitted to the NCHA Data Operations Manager. Probabilistic linkage software will be used to match identifying information from the cohort with the same identifiers held within the NCHA data platform, housed within the Peninsula Health Data Centre. A linkage key (or linkage ID) will be generated for each matched participant and attached to the de-identified records held within the Data Platform. For cases where a 100% probable match is not achieved, a manual review will take place to verify the match. If a case is still uncertain after manual review, the participant will be contacted to verify the match. This will ensure that there are no false positive matches within the dataset. A linkage map, in which the linkage key is mapped to the project ID, will be created and provided to the researcher team so that each individuals’ cohort data can be merged with their de-identified healthcare data. The de-identified data will be transferred to Monash University’s Secure eResearch Platform (SeRP) for storage and analysis.

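### Linked outcomes are declared free of attrition bias, but the linkage covers only Peninsula Health services, so participants who leave the area are lost to it as well

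*Protocol article*

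**What the plan says.** The statement is in the Discussion, Strengths and limitations: "Although outcomes measured through linked data are not subject to bias due to attrition". The sentence goes on to treat attrition as a problem of longitudinal data collection and leads into the retention measures. The same paragraph admits one gap in the linked data, the private hospitals in the region, and proposes to cover it with survey answers. Moving out of the region is not mentioned.

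Other sections bear on the claim:

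- **Coverage (Data-linkage).** The platform supplies "comprehensive healthcare data from all public hospitals, community health and outpatient clinics provided by Peninsula Health", and linkage is "for all attendances to Peninsula Health run services (inpatient and community based"). Setting describes Peninsula Health as the only public provider for this one region.
- **Residence (Participants).** Eligibility requires "residing in either the Frankston or Mornington Peninsula local government areas, with plans to stay in the area". This is a condition at baseline, not during follow-up.
- **Duration.** Data-linkage promises "a minimum of five years for prospective health outcome data". Data collection states: "Participants will be followed up at 12- and 24-months post completion of baseline survey".
- **Death (Data-linkage).** Among the identifiers, "date of death (if applicable) will be extracted from the cohort study contact details database".
- **Analysis (Quantitative data analysis).** "Survival/competing survival analysis will be used to examine risk of and time to key health outcomes", with Poisson or negative binomial models, zero-inflated where needed, for counts such as emergency department admissions.

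**The concern.** The statement would be sound for a source that follows people wherever they live. A regional provider's records do not. Once a participant has left the two local government areas, later hospital care elsewhere produces no linked record, and an attendance dataset shows no record in the same way whether the person was well or was treated somewhere else.

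Two things are at stake. First, absolute rates of linked events are understated if people who have gone are still counted as under observation. Second, the study's exposures include retirement, other life transitions, isolation and loneliness. Some of these could plausibly prompt a move or make a move less likely to be reported. If leaving differs by exposure, comparisons are distorted as well. A team that accepts the sentence as written has no reason to record move dates or define the end of observation, and may later use the linked data to reassure readers about survey dropout. Unrecorded move dates are hard to recover afterwards.

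**Working it through.** The plan attaches no figure to this claim, so there is nothing to reproduce. The check has two parts.

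**1. The claim against the stated coverage**

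- Survey refusal while still resident: linked records continue, so the claim holds.
- Move out of the area: linked records from other providers do not exist in the platform, so the claim fails. A mover who still answers (online or by phone) can report service use in the previous 12 months, but only up to the last wave. A mover who stops answering is lost to both sources.
- Time without a planned survey: 60 − 24 = 36 months of the minimum linked follow-up.

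**2. Size, under assumed leaving rates**

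Inputs: follow-up T = 5 years (the minimum in Data-linkage). The annual leaving rate r is **not in the documents**; 2% to 5% is assumed here. Leaving is taken as exponential, and leavers are taken to be kept at risk with no events seen after departure.

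- Share gone by T: 1 − exp(−rT)
- Share of person-time observable: f(r) = (1 − exp(−rT)) / (rT)
- Apparent rate ratio = true ratio × f(r exposed) / f(r unexposed)

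| r per year | gone by year 5 | f(r) | person-time unobservable |
|---|---|---|---|
| 2% | 1 − exp(−0.10) = 9.5% | 0.0952 / 0.10 = 0.952 | 4.8% |
| 5% | 1 − exp(−0.25) = 22.1% | 0.2212 / 0.25 = 0.885 | 11.5% |

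Rate ratios over five years:

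- Equal leaving in both groups: the factor is 1, so the ratio is unbiased and only absolute rates fall.
- Exposed 5%, unexposed 2%: 0.885 / 0.952 = 0.93. A true 1.00 appears as 0.93, and a true 1.30 as 1.21.
- Exposed 2%, unexposed 5%: 0.952 / 0.885 = 1.08, so the bias can run in either direction.

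Over two years, 5% against 2% gives a factor of 0.97, so most of the problem builds up after the surveys end.

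A cross-check uses the plan's own attrition allowance of 200 in 1000. If a share s of those 200 had left the area, spread evenly over the first two years, each would lose on average 4 of 5 years. The person-time lost is 0.20 × s × 4/5, or 4% at s = 25% and 16% at s = 100%. The share s is again an assumption.

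**The case against.** The strongest defence is that the clause, read in context, contrasts passive linkage with loss from surveys, and in that sense it is right. Moreover, rules for ending observation are normally left to an analysis plan, which is not shown here, and survival methods with competing events can accommodate censoring. This stands in part. It removes several stronger readings that a reader might infer:

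- **That leavers and the dead will remain in the data as event-free.** The article states no rule for the end of observation. The figures above show what happens if they are kept at risk, not what the plan says will happen.
- **That the intention to stay is the only safeguard.** Cohort maintenance describes locator details, including secondary contacts, updated at each wave, and newsletters twice a year that invite updates. Table 1 lists geographical location among the items collected at all three time points. These measures help, but they mainly reach people who respond or volunteer the news.
- **That a death elsewhere is known only if someone tells the team.** Data-linkage says cohort identifiers, date of death among them, are matched with the same identifiers held in the platform, so the platform may hold deaths too. How it obtains them is not stated. Ascertainment is uncertain, not shown to fail.
- **That ratios could be far more distorted.** Leaving at 10% against 2% a year would turn 1.00 into 0.83, but it implies that 1 − exp(−0.50) = 39% of one group has gone by year 5, among people enrolled because they plan to stay. Nothing in the documents supports such a rate.

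The stated power calculations also rest on survey measures of depression, social support and loneliness, so they are unaffected.

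The unqualified wording is not rescued. The limitation paragraph concedes only private care within the region. Censoring known moves would reduce the problem but would not make the sentence true, since leaving may itself be related to health or isolation, and some moves will never be known.

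**Conclusion.** The sentence is wrong as written. It is true of survey non-response alone and untrue of departure from the catchment, given the coverage that the article itself describes and the gap between 24 months of surveys and at least five years of linkage.

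The size cannot be derived from the documents. Under assumed leaving of 2% to 5% a year, with leavers kept at risk, absolute five-year rates are understated by 4.8% to 11.5%. Ratios are biased only if leaving differs by exposure: about 0.93 for a true 1.00 at 5% against 2%. The requirement to plan to stay, and the statement in the Background that most residents use local services, suggest that the bias may be modest. The case for acting now is that the correction is cheap and move dates are best recorded as they happen.

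**What to change.** 1. **Correct the sentence.** For example: linked outcomes are not lost when a participant stops answering surveys, but they are observed only while the participant uses Peninsula Health services; moving out of the area, and deaths that may not be ascertained, limit the linked data.
2. **Define at-risk time for linked outcomes.** End it at known move-out, treat death as a censoring or competing event according to the analysis, and use log person-time as the offset in count models.
3. **Collect the date.** Add a move-date item to the geographical-location question already asked at each wave.
4. **Check residence.** Use the existing locator, secondary-contact and newsletter contacts, including after month 24.
5. **Handle unknown residence by sensitivity analysis.** For example, compare censoring at the last contact that does not depend on the outcome with keeping the participant at risk. Attendance at a Peninsula Health service should not define the end of follow-up: it depends on the outcome, so attenders would gain at-risk time and healthy non-attenders would be cut short.

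Cost: a change of wording, one survey item and a short residence check added to existing contacts. The price in the analysis is slightly less person-time and slightly wider intervals.

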### Setting

The cohort will be recruited from Frankston and the Mornington Peninsula, two adjacent local government areas within Victoria, Australia (see Fig. 2). This area has been strategically chosen for its rich geographic and socioeconomic diversity. The area has a combined population of approximately 310,000 people, with over a quarter (estimated 80,019 people) being aged 50–70 years [21, 22]. The area contains both public and private hospitals, with Peninsula Health being the sole public health provider for the region and managing four hospitals (2 acute with emergency departments and 2 subacute hospitals) and over 10 community and outpatient services, incorporating services such as mental health, community rehabilitation and palliative care. There are five private hospitals in the area, one of which has an emergency department [25, 26].

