### Cohort maintenance

To support cohort retention, a locator form will be used to collect contact information including primary and secondary contact details, preferred method of contact and preferred time of contact, upon completion of the baseline survey and updated at each ‘wave’. Details will be stored in a second secure database separate from survey responses.

Additional maintenance methods will include personal communication with participants, with each participant talking directly to a study team member at least once post baseline. Twice a year Beyond 50 newsletters will be distributed to keep participants up to date on study findings, to maintain interest and promote continuation and provide participants an opportunity to contact the study team to update their contact details.

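### Linked outcomes are declared free of attrition bias, but that holds only for survey non-response: participants who move away, or die elsewhere after contact is lost, are lost to linked follow-up too

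*Protocol article*

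**What the plan says.** All references are to the protocol article.

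- **Strengths and limitations** states, without qualification, that "outcomes measured through linked data are not subject to bias due to attrition". It then turns to survey attrition and the retention measures.
- **Data-linkage** defines the coverage: survey data are linked "for all attendances to Peninsula Health run services (inpatient and community based"). The linked record is to supply "a minimum of five years for prospective health outcome data". Among the identifiers sent for matching, "date of death (if applicable) will be extracted from the cohort study contact details database".
- **Participants** asks only that people live in one of the two areas at baseline and intend to remain. **Background/introduction** says that most residents, not all, use services within the area.
- **Data collection** plans surveys at baseline, 12 and 24 months.
- **Cohort maintenance** says locator details are collected "upon completion of the baseline survey and updated at each" wave, and that a twice-yearly newsletter gives participants a chance to correct their contact details. **Table 1** ticks the Locator Form at baseline only, although it asks about geographical location at all three waves.
- **Quantitative data analysis** plans Poisson or negative binomial models (with zero-inflated variants) for outcomes such as emergency department use, and survival or competing-risk models for time to key outcomes.

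**The concern.** The platform holds the records of one public provider serving two local government areas; it is not a statewide or national register. Someone who stops answering surveys but stays in the area still generates linked records, so the claim is right for that kind of attrition. Someone who moves away generates no further records there, and in the data looks the same as a resident who needed no care. For a single-provider source, moving out is loss to follow-up.

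The study is built around transitions such as retirement, in a region described as a popular retirement destination. Relocation is plausibly related to those transitions and to health and social circumstances. Loss of this kind could therefore differ between exposure groups and distort rate and hazard ratios in the count and survival models. It would also add zeros to count outcomes for which zero-inflated models are already planned.

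The statement matters beyond its wording. A team that believes linked outcomes cannot suffer attrition bias has no reason to establish when people left, or to end their time at risk at that point.

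**Working it through.** The article attaches no figure to this claim, so there is nothing of its own to reproduce. The check has two parts.

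**1. Can the plan see people leave?**

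- Surveys cover 24 months of at least 60 months of prospective linkage: 2/5 = 40%. For at least three years no planned survey would show a move.
- Sample size calculations allows 200 of 1000 participants to be lost, so retention is (1000 - 200)/1000 = 80%. The location item in Table 1 records moves only for people who respond.
- The newsletter contact update depends on the participant replying.
- Whether locator details are refreshed after baseline is unclear, because Table 1 and Cohort maintenance disagree.
- Date of death is passed on from the study's contact database if it is known. No death registry is named. A death elsewhere after contact has been lost may go unrecorded.

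Moves and deaths are thus observable for responders during the first two years, and only patchily for others or later.

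**2. How large could the effect be?**

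The documents give no leaving rate, so every rate below is assumed. Assume a constant leaving rate l per year over five years, no events recorded after leaving, and no censoring. The share of person-time actually observed is

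(1 - exp(-5l)) / (5l)

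| Assumed leaving rate | Share observed | Person-time lost |
|---|---|---|
| 2% a year | 0.952 | 4.8% |
| 3% a year | 0.929 | 7.1% |
| 4% a year | 0.906 | 9.4% |
| 6% a year | 0.864 | 13.6% |

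At 4% a year, 1 - exp(-0.2) = 18.1% have left by year 5, and an uncensored event rate would be about 9% too low.

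For a comparison, observed rate ratio = true rate ratio × (share observed in exposed) / (share observed in unexposed):

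- 6% a year in exposed, 2% in unexposed: 1.00 × 0.864/0.952 = 0.91.
- Equal leaving: the shares cancel and the ratio is unchanged.

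A cruder model gives a similar size. If 20% of the exposed and 5% of the unexposed leave evenly over the five years, the shares observed are 1 - 0.20/2 = 0.90 and 1 - 0.05/2 = 0.975. A true ratio of 1.00 then shows as 0.90/0.975 = 0.92. With the groups reversed it shows as 0.975/0.90 = 1.08. The bias can go either way.

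**The case against.** The strongest reply is that the sentence is being read too widely. It introduces a paragraph on survey attrition, and the sample size section uses the word for loss from the survey sample. In that sense the claim is sound, and the clause itself fixes no analysis. This explains the wording but does not rescue it. The statement is unqualified, out-migration is nowhere named as a limitation, and the design lacks the property claimed.

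Several stronger readings are tempting, and the article does not support them.

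- **That leavers are kept in the denominator as event-free.** No such rule is stated. Survival methods are planned, and censoring dates and offsets may be set in an analysis plan that is not shown. Their absence from the article is not a finding.
- **That private care is overlooked.** It is disclosed: "the NCHA Data Platform only captures data for the public health system and not for the private hospitals in the region". It is incomplete capture rather than attrition, and the survey is meant to measure private emergency and hospital use. The volume argument, "expected to represent a very small number of emergency visits compared to the local public health system", concerns emergency visits only, whereas Setting notes that "There are five private hospitals in the area, one of which has an emergency department". What remains is narrow: the survey check depends on responders and ends at 24 months.
- **That the contact database is the only source of deaths.** Date of death is among the identifiers matched against those held in the platform, which implies that the platform holds it too.
- **That moves go unrecorded throughout.** The location item at each wave and the newsletter both help. The gap is non-responders and the years after month 24.
- **That the ten-year look-back treats recent arrivals as having had no illness.** No analysis described does so.

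**Conclusion.** The point stands in a limited form. The article attributes to the linked outcomes a property that holds for survey non-response and fails for out-migration and for deaths elsewhere after contact is lost. That follows from its own account of coverage, eligibility and follow-up length, and would hold whatever an unseen analysis plan says.

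The possible consequence is bias in linked rate and hazard ratios if leaving differs between the groups compared; the documents do not show that it does. The illustrative sizes (7-14% of five-year person-time at 3-6% leaving a year; a null ratio shown as about 0.91 at 6% versus 2%) rest on assumed constant leaving rates, no censoring, and no later care at the local provider. No figure printed in the article is shown to be wrong.

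The disagreement between Table 1 and Cohort maintenance is minor in itself, but it concerns the information needed to date a move.

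**What to change.** 1. **Reword the claim.** Say that linked outcomes are unaffected by survey non-response as such, but remain open to out-migration, unrecorded death and care outside Peninsula Health.
2. **Define time at risk for linked analyses.** In count and survival models, end it at the date of leaving, death or last confirmed residence. Residence may be confirmed by the survey location item, a locator update, newsletter or phone contact, or the platform address. Where competing-risk models are used, a death that is itself a competing event should be coded as one. Use log person-time as the offset in count models.
3. **Add a sensitivity analysis without this censoring**, to show how far results depend on it. This matters because last confirmed residence itself depends partly on contact, and a platform address may be refreshed only when someone attends.
4. **Reconcile Table 1 with Cohort maintenance** on whether the Locator Form is updated at each wave.
5. **Use the existing newsletter contact update to confirm residence** for as long as linkage runs.
6. **Add one sentence on private care:** the survey check covers responders only and ends at 24 months.

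The cost is wording, a table correction and a residence question in a mailing that would have to continue beyond the survey waves. The statistical price is somewhat less person-time and slightly wider intervals. Censoring corrects the denominator for people whose departure is known; it does not recover care received elsewhere, and it still assumes that leaving is unrelated to outcome given the covariates in the model.
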